### Intervention

#### Overview

Participants in the intervention group will be provided e-learning about dementia risk reduction and promoting brain health (Figure 3), consisting of the following components: (1) one 35-minute multimedia e-learning lesson on promoting brain health and preventing dementia and (2) a series of 12 “microlearning” emails (3 emails per week) with small segments of content to reinforce the material from the lesson. Participant progress is saved, so they can return to the lesson to complete it at another time. Participants will have 4 weeks to complete the intervention.

The lesson will be delivered through the Division of e-Learning Innovation’s learning management system to record participants’ access, progress, and completion of the lessons. This allows us to measure the “dose” of educational exposure to the intervention and to provide automated timed reminders to encourage participants to complete the lesson.

**Figure 3 figure3:**
[figure not shown]
DementiaRisk intervention group e-learning lesson.

#### Microlearning Emails

In addition to the lessons, participants will also receive 3 microlearning emails per week with a small amount of content that reinforces the information from the lessons. This spaced repetition has been shown to benefit knowledge transfer [6]. Content for the emails will be taken directly from the promoting brain health e-learning lesson.

### Control Condition

Participants randomized to the control group will be provided e-learning about mild cognitive impairment, consisting of the following components: (1) one 20-minute multimedia e-learning lesson on mild cognitive impairment and (2) a series of 12 “microlearning” emails (3 emails per week) with small segments of content to reinforce material from the lesson.

### Outcomes

#### Overview

Primary and secondary outcomes will be assessed at baseline (T1), at 4 weeks (T2), and at 2 months after the intervention (T3). Qualitative data will be collected at 4 weeks (T2; Multimedia Appendix 2). Participants will access web-based surveys through the password-protected research platform hosted by the Division of e-Learning Innovation. Participants will be required to complete all components of the intervention. Surveys will not be submitted unless the participant completes all questions. Participants will not be able to change their answers after submitting and will not be able to submit multiple attempts.

#### Primary Outcome

The primary outcome measure of this study is knowledge change related to dementia risk factors. Knowledge of dementia risk factors will be assessed using a custom 15-item multiple-choice assessment aligned with the content of the intervention as well as the risks and health promotion subdomain of the Dementia Knowledge Assessment Scale [13]. Response options are “false,” “probably false,” “probably true,” “true,” and “I don’t know.” The total maximum score for this assessment is 30 (maximum 2 points per question), with higher scores indicating higher levels of knowledge related to dementia risk factors. Individual scoring is as follows: (1) 2 points for answering “true” to a true question, (2) 2 points for answering “false” to a false question, (3) 1 point for answering “probably true” to a true question, (4) 1 point for answering “probably false” to a false question, (5) 0 points for answering “probably false” or “false” to a true question, (6) 0 points for answering “probably true” or “true” to a false question, (7) 0 points for answering “I don’t know.”

#### Secondary Outcomes

Secondary outcome measures include (1) intentions to engage in health behaviors in line with evidence will be assessed using a 10-item Likert scale–based survey and a composite score and (2) health behaviors related to behavior change for modifying dementia risk factors will be assessed using the Godin-Shephard Leisure Time Physical Activity Questionnaire along with additional questions related to a range of health status and behavior domains including diet, smoking, alcohol consumption, social activity, traumatic brain injury, blood pressure, depression, air pollution, diabetes, sleep habits, cognitive activity, and hearing to determine a composite score. Where possible, these questions were selected from validated tools (Multimedia Appendix 2). Additional data will be collected on engagement with the web-based intervention throughout the study, including (1) e-learning analytics: progress or completion, login activity, and time on the lesson and (2) email campaign analytics: open rate and click-through rate.

#### Qualitative Data

Qualitative data will be collected through structured survey questions and open-ended questions. The effectiveness and impact of the intervention will be assessed using the Information Assessment Method for patients and consumers, a validated questionnaire that assesses outcomes of web-based consumer health information [14]. End-of-intervention and poststudy surveys will include open-ended questions to assess participant satisfaction with the intervention, changes in attitudes, beliefs, and behaviors during the study, and feedback on proposed future dissemination methods.

### Data Analyses

#### Overview

All outcome assessors and data analysts will be blinded to participant allocation. The CONSORT (Consolidated Standards of Reporting Trials) extension for randomized pilot and feasibility trials and CONSORT-EHEALTH [15-17] will guide reporting of the study. The 12-item TIDieR (Template for Intervention Description and Replication) checklist was used for the intervention description [18]. Qualitative reporting will adhere to the COREQ (Consolidated Criteria for Reporting Qualitative Studies) [19].

#### Quantitative Data

All data will be entered into RStudio (version 2022.02.3; Posit PBC) [20-22]. A linear mixed effects model will be used to examine the relationship between total knowledge score and group by time point. The same model will be used to look at health behavior scores and total intention scores. We will look at outcome scores from all 3 time points (baseline [T1], at 4 weeks [T2], and at 2 months after the intervention [T3]). The stratification variables, age and level of education, will be included in all models. Additionally, we will examine possible effect modifiers of age, sex, and education on the relationship between groups and outcomes as well as time point and outcomes. For knowledge scores specifically, we will look at a family history of dementia or having been a care partner of a person living with dementia as a possible effect modifier of the relationship between group and knowledge score and time point and knowledge score. These models will be run for both intention-to-treat and per-protocol participant data.

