#### Randomization and Allocation Concealment

Participants will be randomized and directed to their assigned group after submitting web-based informed consent using the Division of e-Learning Innovation’s research platform. Participants will be randomized using a permuted block stratified randomization, using education and age as the stratification variables. Our stratified block randomization approach will be based on the following components: (1) level of education: we will stratify participants based on educational background or highest level of education completed: “high school or equivalent,” “some college or university,” and “college or university graduate or graduate degree” and (2) age: we will stratify participants based on ages: “younger than 45 years,” “45-65 years,” and “older than 65 years.”

To ensure a balance between the intervention and the control groups, we will use stratified block randomization with variable block sizes of 4, 6, and 8 (randomly arranged) in a ratio of 1:1. To the best of our ability, efforts will be made to blind participants to their allocation group and study hypotheses. We will ensure that promotional advertisements do not contain logos or direct website links. The informed consent form will not contain the exact outcome measures or the title of the intervention. Allocation concealment will be aided by referring to the intervention as “e-learning related to cognitive impairment and dementia prevention” without biasing participants to study hypotheses or study design.

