#### Sample Size Calculation

Using a conservative estimate of a small effect size (0.16, from a meta-analysis of internet health behavior change interventions), with a power of 0.80 and α of .05, we require a total of 388 participants in the study [10,11]. To allow for a 25% dropout rate, we aim to recruit 485 individuals [10,11]. These recruitment numbers and strategies have been used successfully in similar knowledge translation intervention studies and are a feasible target, given the use of the paid panel [12].

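### The mixed model, as described, takes the baseline score as a repeated outcome and not as a covariate; on the natural reading this is valid but gives up precision that a common baseline mean would recover

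*Protocol article*

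**What the plan says.** All references are to the protocol article.

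- **Primary Outcome:** "The primary outcome measure of this study is knowledge change related to dementia risk factors".
- **Quantitative Data, model:** "A linear mixed effects model will be used to examine the relationship between total knowledge score and group by time point". The same model serves the intention and health behaviour scores.
- **Quantitative Data, responses:** "We will look at outcome scores from all 3 time points", and baseline (T1) is listed as one of the three.
- **Quantitative Data, covariates:** "The stratification variables, age and level of education, will be included in all models". The baseline score is not named as a covariate.
- **Sample Size Calculation:** "Using a conservative estimate of a small effect size (0.16, from a meta-analysis of internet health behavior change interventions"), and "with a power of 0.80 and α of .05, we require a total of 388 participants in the study".

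The article does not say whether the arms share a baseline mean, which time point or contrast is primary, or what within-person covariance is used. It gives no SD and no correlation between baseline and follow-up. Randomisation follows consent, but the text does not place the T1 survey before or after assignment, and the flow figure is not shown.

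**The concern.** A group-by-time model with T1 among the responses, fitted in the usual way, estimates a separate T1 mean for each arm. With the primary outcome defined as change, the treatment effect is then the between-arm difference in mean change from T1 to T2 or T3. This subtracts the whole observed baseline difference between arms. Under randomisation any such difference is chance, and the efficient correction subtracts only the part that predicts follow-up. Full subtraction adds noise.

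The baseline score is collected anyway and is probably a strong predictor of the follow-up scores. Recruitment has closed, so more participants cannot supply precision, but the analysis still can. The same model is used for three outcomes, so the loss would apply to all of them.

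**Working it through.** **Inputs.** From the article: 1:1 allocation, three time points, effect size 0.16, alpha .05, power 0.80, 388 required, 485 recruited. Assumed, because the article does not give them: a two-sided test; 0.16 read as a difference in units of the raw-score SD; rho, the baseline-to-follow-up correlation after adjustment for age and education, between 0.4 and 0.8.

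**The plan's own figure.** The article states no precision figure to reproduce. Its sample size does not follow from d = 0.16 in a two-arm comparison of means: 2 × (1.960 + 0.842)² / 0.16² = 613.3, so 614 per arm or 1,228 in total, against 388. Read instead as Cohen's f = 0.16 (d = 0.32), the total is 308 to 309.

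**Step 1: complete data, equal SDs.** Take the SD as 1. The variance of the contrast is proportional to

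- arm-specific baseline means: 1 + 1 - 2·rho = 2(1-rho);
- common baseline mean, or baseline as covariate: 1 - rho².

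The reduction is 1 - (1-rho²)/[2(1-rho)] = (1-rho)/2.

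**Step 2: missing follow-up.** If a fraction p of participants has follow-up and everyone has T1, the free model's variance is proportional to (1-rho²)/p + (1-rho)², and the constrained model's to (1-rho²)/p. The reduction is (1-rho)/[(1+rho)/p + (1-rho)]. The table uses p = 0.75, with all loss before T2.

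**Step 3: power.** At 194 per arm, d·√(n/2) = 0.16 × √97 = 1.576. Divide by the square root of each Step 1 variance, subtract 1.960 and take the normal probability.

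| rho | 2(1-rho) | 1-rho² | Reduction, complete data | Reduction, p = 0.75 | Power, free baseline | Power, common baseline |
|---|---|---|---|---|---|---|
| 0.4 | 1.20 | 0.84 | 30% | 24% | 30% | 40% |
| 0.5 | 1.00 | 0.75 | 25% | 20% | 35% | 44% |
| 0.6 | 0.80 | 0.64 | 20% | 16% | 42% | 50% |
| 0.7 | 0.60 | 0.51 | 15% | 12% | 53% | 60% |
| 0.8 | 0.40 | 0.36 | 10% | 8% | 70% | 75% |

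If half of a 25% loss falls before T2 and half between T2 and T3, the reductions at rho 0.5 are 23% at T2 and 20% at T3.

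The planned 25% loss from 485 leaves 485 × 0.75 ≈ 364, or 182 per arm. At rho 0.5, 0.16 × √91 = 1.526 gives 33% power, and 1.526/√0.75 = 1.762 gives 42%. A variance ratio of 0.75 is worth 1/0.75 = 1.33 times the sample.

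**Step 4: unequal SDs.** Let s be follow-up SD divided by baseline SD. With complete data the reduction is (1 - rho·s)² / (1 + s² - 2·rho·s). It is never negative and is zero when rho·s = 1.

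| s | rho 0.4 | rho 0.6 | rho 0.8 |
|---|---|---|---|
| 0.8 | 46% | 40% | 36% |
| 1.0 | 30% | 20% | 10% |
| 1.2 | 18% | 8% | 0.3% |

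**Step 5: a different contrast.** If the analysts took the plain follow-up difference from the free model, and not the change, the reduction would be rho²: 16% at rho 0.4 and 64% at rho 0.8 with complete data. The conclusion would hold, but the size would differ.

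**The case against.** The strongest reply is that the article never says the baseline means are free. A constrained longitudinal model also takes T1, T2 and T3 as responses with group-by-time terms, so the sentences quoted fit it too. The parameterisation of the baseline term is a detail that a condensed article may leave to a fuller analysis plan, and that plan is not shown. Even if the means are free, the model is standard and introduces neither bias nor an inflated type I error.

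Much of this stands. A reader might infer that the article states arm-specific baselines; it does not, and the reading here is an inference. It is still the natural one: the primary outcome is change, adjusters are listed for all models without the baseline score, and omitting the group effect at T1 is a deliberate step of which the text gives no sign. A reader might also infer that the planned analysis is wrong; it is not.

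The reply does not show a setting where the free model gives a more precise change contrast. In large samples Step 4 shows none.

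Two further limits stand. The common-baseline constraint needs T1 to be unaffected by assignment, which the Randomization and Allocation Concealment section does not establish. And the Results section reports analyses as ongoing after data collection ended, so a change of primary model now needs care.

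**Conclusion.** The point holds as one of efficiency, not validity. On the natural reading, the plan uses the baseline score less well than it could. The gain from a common baseline mean is 30% to 10% of the variance of the change contrast, on three assumptions: rho of 0.4 to 0.8, equal SDs and complete data. With 25% missing follow-up it is about 24% to 8%. With follow-up SDs 0.8 to 1.2 times the baseline SD it runs from 46% to almost nothing.

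Two stronger conclusions are tempting and unsupported. The first is that 10% to 30% is a fixed gain to be had at no cost: the article supplies no rho or SD, and the condition on T1 timing is open. The second is that the change repairs the sample size. Under d = 0.16 and 388 analysed, power with the constraint is still 40% to 75% for rho 0.4 to 0.8. The required total with baseline adjustment is 443 at rho 0.8, and falls below 388 (to 383) only at about rho 0.83.

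**What to change.** 1. Name the primary contrast (T2 or T3) and state how baseline is handled.
2. Confirm that T1 is completed before assignment is revealed.
3. If it is, fit for knowledge, intentions and behaviours a mixed model with time (T1, T2, T3), group-by-T2 and group-by-T3 terms, no group effect at T1, the stratification variables as covariates, and an unstructured within-person covariance. The alternative is to model T2 and T3 with the baseline score as a covariate. It gives similar results, but participants with only a T1 score drop out of it.
4. Record the choice, with a date, before the analysts are unblinded. If that moment has passed, keep the planned model as primary and report this one as a sensitivity analysis.

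The cost is a line in the analysis plan and a small change to the model code. No new data are needed. The sample size needs separate attention.

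### Read naturally, the mixed model's age and education terms drop out of the change-from-baseline contrast on complete data; adding their interactions with time point would be a minor gain in precision and SE calibration

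*Protocol article*

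**What the plan says.** Randomization and Allocation Concealment stratifies by three education levels and three age bands: "Participants will be randomized using a permuted block stratified randomization, using education and age as the stratification variables". Blocks are of "variable block sizes of 4, 6, and 8 (randomly arranged) in a ratio of 1:1".

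Primary Outcome defines the endpoint as a change: "The primary outcome measure of this study is knowledge change related to dementia risk factors". Under Quantitative Data, the model is given as: "A linear mixed effects model will be used to examine the relationship between total knowledge score and group by time point". Baseline is one of the modelled outcomes: "We will look at outcome scores from all 3 time points".

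The strata are then brought in: "The stratification variables, age and level of education, will be included in all models". The next sentence, introduced as something additional, says "we will examine possible effect modifiers of age, sex, and education on the relationship between groups and outcomes as well as time point and outcomes".

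The article does not state whether age and education enter as main effects only or also by time point. It does not name the coefficient that is the treatment effect, and it does not say whether the baseline means of the two groups are constrained to be equal.

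**The concern.** Age band and education level do not vary within a person. As main effects they shift that person's T1, T2 and T3 scores by the same amount, and a difference between two of those scores removes the shift. If the treatment effect is the group difference in change since T1, main effects for the strata may do nothing to it, although the evident purpose of including them is to let the analysis reflect the stratified randomisation.

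At stake is mainly the SE. Stratified blocks balance the strata between arms, so part of the variation in change no longer contributes to the sampling error of the group contrast. A model that leaves this part in the residual reports an SE that is too large, the test runs below its nominal 5%, and some power is lost. The size depends on how far age and education predict change in knowledge, for which the article gives no figure.

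**Working it through.** **Inputs.** From the protocol article: outcomes at T1, T2 and T3; 1:1 allocation in stratified blocks; 3 × 3 = 9 strata; 388 participants required, power 0.80 and α .05 (Sample Size Calculation). The plan has no figure of its own on this point to reproduce; 388 and 80% serve only as reference values. Assumed: the share R² of the variance of change that the strata explain, at 2%, 5% or 10%; a two-sided test; and the means and SDs of the simulated scores.

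**Step 1: the cancellation.** Write the mean score of person i at time t as β_t + γ_t·g_i + δ′x_i, where g is group and x holds the age and education indicators. Let D_t be the raw group difference at time t and Δx the group difference in mean x. On complete data, for any value of δ, the fitted γ_t is D_t − δ′Δx. The change contrast is therefore

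(D_2 − δ′Δx) − (D_1 − δ′Δx) = D_2 − D_1,

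the same as with no strata terms.

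**Step 2: fitted models.** Mixed models on simulated complete data (N = 388; strata assumed to shift change by 1.5 points per level) gave for group-by-T2:

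| Model | Estimate | SE |
|---|---|---|
| Random intercept, no strata | 1.507709 | 0.385506 |
| Random intercept, strata main effects | 1.507709 | 0.385506 |
| Random intercept, strata by time | 1.759956 | 0.360881 |
| Unstructured covariance, no strata | 1.549820 | 0.419908 |
| Unstructured covariance, strata main effects | 1.549820 | 0.419908 |

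The unstructured fits use a separate simulated data set. The SE with strata by time is 0.360881/0.385506 = 0.936 of the other, about 6% smaller. The estimate moves because allocation in this simulation was not stratified; in the trial the shift would be smaller.

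With strata that do not affect change, the SE was 0.369747 without strata or with main effects and 0.372089 with strata by time, a ratio of 1.006.

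**Step 3: type I error.** Under stratified blocks the true variance of the contrast is about (1 − R²) times the variance that the unadjusted model reports. Simulated variance ratios (adjusted to unadjusted) with blocks of 4, 6 and 8 were 0.980, 0.951 and 0.900. The true two-sided error is 2·[1 − Φ(1.96/√(1 − R²))]:

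- R² = 2%: 1.96/0.98995 = 1.980, giving 4.8%
- R² = 5%: 1.96/0.97468 = 2.011, giving 4.4%
- R² = 10%: 1.96/0.94868 = 2.066, giving 3.9%

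**Step 4: power.** Take an effect with 80% nominal power at the unadjusted SE, so effect/SE = 1.96 + 0.8416 = 2.8016. The unadjusted test already has the smaller true variance, so its power is Φ(0.8416/√(1 − R²)). The adjusted test has Φ(2.8016/√(1 − R²) − 1.96).

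| R² | Unadjusted | Adjusted | Gain (points) |
|---|---|---|---|
| 2% | 80.2% | 80.8% | 0.5 |
| 5% | 80.6% | 82.0% | 1.4 |
| 10% | 81.2% | 84.0% | 2.7 |

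Gains are taken before rounding.

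**Step 5: where the cancellation is not exact.** In the same setting as the random-intercept rows of Step 2, with some participants missing both T2 and T3, the estimate is 1.4486 (SE 0.4352) without strata, 1.3886 (SE 0.4334) with main effects and 1.6005 (SE 0.4078) with strata by time. With complete data and a common baseline mean it is 1.3466 (SE 0.3567) without strata and 1.3827 (SE 0.3440) with main effects. Main effects then do some adjusting. With dropout, strata by time still gives the smaller SE.

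**The case against.** **The reading is inferred.** The article never says that the strata are main effects only, and it names no contrast. It condenses a fuller document, which may specify both. This stands, so the point is conditional. It still concerns stated text: the article sets a rule for all models and lists the strata's relation to time as an additional effect-modifier analysis, which would be redundant if those terms were already in the main model.

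**The strata-by-time terms are already planned.** They are, but as an exploration of effect modifiers, and nothing ties them to the primary comparison.

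**A reader might infer that the primary comparison is wholly unadjusted or confounded by age and education.** The documents do not support that. A change contrast already removes any constant stratum effect, the blocks keep the strata balanced, and exact cancellation needs complete data and unconstrained baseline means. The plan allows for 25% dropout.

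**A reader might infer material bias from dropout.** That requires dropout that differs by arm within education levels and an education effect on change. With an assumed 45% versus 25% dropout by arm in a low-education third (20% elsewhere) and a 2-point difference in change, simulation gave a mean error of 0.17 points without strata, 0.09 with main effects and 0.00 with strata by time, on a 30-point scale. The article supports none of these inputs. Where dropout did not differ by arm, all three models were unbiased.

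**A reader might infer that strata-by-time terms are needed however baseline is handled.** They are not. Under a common baseline mean, main effects alone reduced the SE (Step 5).

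**The error is conservative.** This also stands: the risk is lost power, not false positives.

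**Conclusion.** The point holds as a minor one. If the model is group by time point with T1 as an unconstrained outcome and strata as main effects, the strata terms leave the change-from-T1 contrast and its SE unchanged on complete data. The estimate remains essentially unbiased. If the strata explain 2% to 10% of the variance of change, the test runs at about 4.8% to 3.9% instead of 5%, and adjustment would add about 0.5 to 2.7 points of power. If they explain none, there is nothing to gain. That range is an assumption, since the documents give no value. The recommendation improves precision and the calibration of the SE; it does not correct a material bias.

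**What to change.** In Quantitative Data, and in the analysis plan, state that age and education, together with the interaction of each with time point, will be included in all models. In the same place, name the group contrasts at T2 and at T3 as the treatment effect. If the full analysis plan already specifies this, the sentence merely records it.

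The cost is eight fixed-effect parameters (2 factors × 2 indicators × 2 follow-up times) against 388 participants, with no new data. If the strata turn out not to predict change, the penalty is negligible: the SE rose from 0.3697 to 0.3721 in the check above. The Results section says that analyses are ongoing, so the choice should be dated and settled before unblinding, and any departure from the existing plan reported.

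### The effect-modifier analyses address group–outcome and time–outcome relationships, not the group-by-time effect that the model uses: one is a diluted test, the other pools both arms

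*Protocol article*

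**What the plan says.** All the relevant text is in the protocol article, Methods, mostly under Data Analyses, Quantitative Data.

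- **Main model:** "A linear mixed effects model will be used to examine the relationship between total knowledge score and group by time point". The same model serves the intention and health-behavior scores. Scores from baseline (T1), T2 and T3 all enter as outcomes; baseline is not named as a covariate.
- **Primary outcome** (Primary Outcome section): "The primary outcome measure of this study is knowledge change related to dementia risk factors".
- **Covariates:** "The stratification variables, age and level of education, will be included in all models".
- **Effect modifiers, all outcomes:** possible "effect modifiers of age, sex, and education on the relationship between groups and outcomes as well as time point and outcomes".
- **Effect modifiers, knowledge only:** family history of dementia or care-partner experience "as a possible effect modifier of the relationship between group and knowledge score and time point and knowledge score".

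No model formula is written out. Reading these sentences as modifier × group and modifier × time terms is the natural reading of the prose, not a quoted specification.

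**The concern.** With baseline among the outcomes, and the primary outcome defined as change, the intervention effect is the group-by-time contrast. Whether it differs by subgroup is then a question about modification of that contrast. Both modifier sentences instead separate group from time, and neither names modification of the combined effect. The main-model sentence does join the two, so the article's own sentences do not match.

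Two consequences follow if the wording is carried out.

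- A modifier × group term averaged over T1 to T3 includes a baseline contrast at which no intervention effect can exist, so a real subgroup difference is understated.
- A modifier × time term pools the arms. Older or less educated participants may simply gain more or less from retaking the same 15-item knowledge test. That result would appear under the label of effect modification although it says nothing about the intervention.

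**Working it through.** The article gives no figure for these analyses, so there is none to reproduce.

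**Inputs from the article:** two arms, 1:1; three time points with baseline as an outcome; 388 participants (Sample Size Calculation).

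**Assumptions, not in the article:** SD 1; compound symmetry with within-person correlation ρ (0.3 to 0.7 shown); binary 50/50 modifier; complete data; true subgroup difference in intervention effect δ, equal at T2 and T3 and zero at T1; δ = 0.5 SD for power, two-sided .05.

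**1. What each term estimates**
- Modifier × group over T1–T3: (0 + δ + δ)/3 = 0.67δ.
- Modifier × time, mean(T2,T3) − T1, arms pooled 1:1: (0 + δ)/2 = 0.50δ.
- Modifier × group × time, mean(T2,T3) − T1: δ.
- Modifier × group on mean(T2,T3), baseline-adjusted: δ.

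If 25% of participants drop out after baseline (the article gives the 25%; the timing is assumed), generalized least squares gives baseline more weight. Modifier × group then recovers 0.75 × 2 / [0.75 × 3 + 0.25(1 + 2ρ)] = 1.5 / [2.25 + 0.25(1 + 2ρ)] of δ: 0.60 as ρ approaches 0 and 0.53 at ρ = 0.7.

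**2. Precision and power**

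The variance of each group-by-modifier contrast is its per-person variance times 16/388 = 0.0412.

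| Contrast | Per-person variance | Estimates | Power, ρ = 0.3 | ρ = 0.5 | ρ = 0.7 |
|---|---|---|---|---|---|
| Modifier × group, T1–T3 | (1 + 2ρ)/3 | 0.33 | 61% | 52% | 45% |
| Modifier × group × time, unconstrained | 1.5(1 − ρ) | 0.50 | 67% | 81% | 96% |
| Modifier × group on T2/T3, baseline-adjusted | (1 + ρ)/2 − ρ² | 0.50 | 91% | 94% | 98% |

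Worked at ρ = 0.5:
- Modifier × group: SE = √(0.667 × 0.0412) = 0.166; 0.333/0.166 = 2.01; power Φ(2.01 − 1.96) = 52%.
- Baseline-adjusted: SE = √(0.50 × 0.0412) = 0.144; 0.50/0.144 = 3.48; power Φ(1.52) = 94%.

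The first two rows cross where (4/9) × 1.5(1 − ρ) = (1 + 2ρ)/3, that is, at ρ = 0.25. Below that, the unconstrained three-way contrast has less power than modifier × group. The adjusted variance factors as (1 − ρ)(1 + 2ρ)/2. Its squared signal-to-noise ratio is therefore 1.5/(1 − ρ) times that of modifier × group and 3/(1 + 2ρ) times that of the three-way contrast. Both exceed 1 for ρ from 0 up to 1.

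**3. Chance baseline imbalance b between arms within a subgroup**

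Such an imbalance regresses to ρb at T2 and T3.
- Modifier × group carries (1 + 2ρ)/3 of b: 0.53, 0.67, 0.80 at ρ = 0.3, 0.5, 0.7.
- Unconstrained three-way carries −(1 − ρ) of b: −0.70, −0.50, −0.30.
- Baseline-adjusted: ρb − ρb = 0.

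**4. Simulation** (3,000 trials per scenario, N = 388, ρ = 0.5)
- No modification: modifier × group rejects in 4.9%.
- True δ = 0.5: modifier × group averages 0.34, modifier × time 0.25, three-way 0.50.
- No modification, but the subgroup's time trend differs by 0.3 SD in both arms: modifier × time rejects in 93%, the three-way contrast in 5%. By formula, SE = √(0.75 × 4/388) = 0.088; 0.3/0.088 = 3.41; power Φ(1.45) = 93%.

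**The case against.** The strongest reply has four parts.

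- **Validity of modifier × group.** A reader might infer that neither term measures effect modification at all. That goes too far. Under randomization modifier × group keeps its 5% error rate and responds to a true difference, so it is valid but diluted. This stands.
- **Baseline imbalance.** A reader might also infer that a chance baseline imbalance passes whole into modifier × group. It does not: the share is (1 + 2ρ)/3, and full carry-over would need a perfectly persistent imbalance. The unconstrained three-way contrast has a sensitivity of its own, larger at ρ = 0.3 (0.70 against 0.53). This stands too, and it decides which remedy to prefer.
- **What the article claims.** The text describes time-point modification as modification of the time–outcome relationship, and does not say that it shows a differential intervention effect. That is fair. The risk lies in how a result labelled effect modification will be read.
- **Condensed prose.** No formula is given, nothing says that a three-way term is excluded, and a fuller analysis plan may contain one. That limits the point to the wording as it stands. It does not remove it: the article states which relationships will be examined, twice and in the same form, and they do not match its own group-by-time effect.

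The number of subgroup tests, and running them on the per-protocol set as well, are separate matters and do not bear on this point.

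**Conclusion.** The point holds in limited form. As written, neither relationship yields an unbiased estimate of whether the group-by-time effect differs by age, sex, education, or family history/care-partner status. Modifier × group over T1–T3 recovers about two thirds of a constant post-baseline subgroup difference with complete data, and somewhat less if dropout follows baseline. Modifier × time cannot be read as modification of the intervention effect.

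The two-thirds figure rests on equal effects at T2 and T3 and complete data, and does not depend on ρ under compound symmetry. The power figures depend on the assumed δ, ρ and 50/50 split. The 93% figure depends on the assumed 0.3 SD trend difference.

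The documents do not support the inference that the subgroup results must be wrong, or that the trial's main result is at risk. These analyses are secondary and the primary comparison is unaffected.

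**What to change.** For age, sex, education and, for knowledge, family history/care-partner status, state that effect modification will be tested as modifier × group on T2/T3 scores. Baseline should be either constrained equal between arms (within modifier levels) or adjusted as a covariate. This is preferred to an unconstrained modifier × group × time term, which is also unbiased but remains sensitive to chance baseline imbalance and is weaker at low within-person correlation.

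Report subgroup-specific intervention effects with 95% CIs and label them exploratory. If modifier × time is kept, describe it as a subgroup difference in change over time across both arms, and do not interpret it as modification of the intervention effect.

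The cost is a change of model term and a sentence of text, with no new data; the article says that analysis is ongoing. The interaction intervals will be wide (at ρ = 0.5, about ±1.96 × 0.144 = ±0.28 SD for a 50/50 modifier with 388 participants), and wider for smaller subgroups.
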